#### Additional and exploratory analyses

Exploratory analyses will incorporate baseline, midpoint, endpoint, and follow-up as covariates or additional outcomes to characterise temporal patterns beyond the primary and secondary endpoints. Bayesian analyses may be conducted as a complementary approach, providing posterior estimates with corresponding credible intervals.

Continuously collected measurements, such as light exposure, might further be explored non-linearly through generalised additive mixed models (GAMMs) [37], which have been shown to be a good fit for personal light exposure data [38]. Additional exploratory analyses will be pre-registered on the Open Science Framework prior to execution to ensure transparency.

#### Interim analyses and stopping guidelines

No formal interim analyses are planned. Stopping criteria will be limited to safety concerns identified by the Steering Committee (e.g., unforeseen adverse events related to device use). Any decision to terminate or modify the trial will rest with the PI in consultation with the Steering Committee and the Institutional Review Board (IRB).

#### Statistical software

Statistical analyses will be conducted using R. Particular R packages that are planned to be used, among others, include *LightLogR* [39] for processing and calculating light data and variables, and *tidyverse* [40] for a stringent, tidy analysis framework.

### Adverse events

The LightSPAN trial is considered minimal risk, as the intervention involves the use of a mHealth application and wearable monitoring devices. There are no known serious harms associated with these technologies. Possible risks include minor discomfort from wearing the ActLumus light logger or Garmin Vivosmart 5 activity tracker. These risks are considered low and are comparable to wearing commercially available wearable devices. No invasive procedures are involved except for dried blood spot collection for vitamin D analysis, which may cause minor discomfort.

#### Systematically assessed adverse events

Participants excluded following ocular health screening will receive a referral letter outlining the findings and recommending follow-up with an appropriate healthcare provider or specialist.

#### Non-systematically assessed adverse events

Participants are encouraged to report any problems or adverse experiences spontaneously to the study team throughout the trial. Reports will be collected via phone, email, or in person during centre visits.

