#### Eligibility criteria

Participants must be capable of independent mobility, with or without assistive devices and demonstrate functional independence as assessed by the Lawton Instrumental Activities of Daily Living (IADL) scale [23], with a score greater than 8 for females and greater than 5 for males. Participants are required to own a smartphone, be proficient in English reading and communication and not be currently enrolled in another mHealth interventional study.

Exclusion criteria include the presence of cognitive impairment, defined as a Montreal Cognitive Assessment (MoCA) [24] score below 26 after education adjustment, or depressive symptoms, defined as a score greater than 6 on the short form of the Geriatric Depression Scale (GDS) [25]. Individuals with significant physical impairments and/or medical diagnoses that interfere with daily activities, severe terminal illness, or psychiatric conditions affecting daily function will be excluded. Participants with visual impairment, diagnosed eye diseases, ocular abnormalities (as assessed by a licensed optometrist), or uncorrected hearing impairment are not eligible.

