##### Allocation concealment and implementation

To guarantee allocation concealment, the allocation sequence will be securely implemented by a research team member who is not in direct contact with the participants.

Participant enrolment is conducted by trained research staff at the partner Active Ageing Centres. Group assignment is performed only after eligibility confirmation and completion of the baseline observation phase. The random allocation sequence is generated by an independent statistician and stored within a secure, central, web-based randomisation module managed by the data management team. Enrolling staff request assignment through this system; the system releases the allocation only at the point of randomisation. Personnel responsible for enrolment and those delivering study procedures have no access to the randomisation list or block details. The master sequence file is access-restricted (statistician and data manager only) and kept on an encrypted server with audit logs.

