### Data collection

Outcome data will be collected using a combination of wearable devices, validated questionnaires, cognitive tests and clinical assessments as outlined in the Outcomes section of this protocol. Light exposure is measured continuously using the ActLumus pendant logger, while rest-activity cycles, sleep and physical activity are recorded using the Garmin Vivosmart 5 tracker. As outlined in Outcomes, validated self-report instruments include the PSQI, BMIS, VAMS, NIH Toolbox cognitive tests and PASE. Frailty measures include grip strength, gait speed, weight loss, exhaustion and activity level. Body composition is assessed using BIA and vitamin D is measured using dried blood spot analysis. Usability and acceptability of the intervention are assessed using the MAUQ, adapted TAM and TFA survey.

To ensure quality, all assessors are trained and certified in administering the questionnaires and performance-based measures. Standard operating procedures are in place for device calibration, biosample handling and data transfer. Data is collected electronically using secure, tablet-based entry systems, with automatic checks for out-of-range or missing values.

Participant retention and completeness of data collection will be supported through regular check-ins, technical support for device use and reminder notifications via the app in both trial arms. Participants who discontinue the intervention will still be invited to complete outcome assessments at scheduled visits unless they withdraw consent entirely. Reasons for non-adherence (e.g. device discomfort, loss of interest) or non-retention (e.g. withdrawal, loss to follow-up) will be systematically documented.

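### The section on systematically assessed adverse events covers no randomised participant; their stated collection route is spontaneous report, so counts will probably be incomplete and a comparison by arm weak

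*Protocol article*

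**What the plan says.** The Adverse events part of the protocol article separates systematic from non-systematic assessment.

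- **Systematically assessed adverse events.** The whole content is one sentence about a letter: "Participants excluded following ocular health screening will receive a referral letter outlining the findings", with advice to seek follow-up care.
- **Non-systematically assessed adverse events.** "Participants are encouraged to report any problems or adverse experiences spontaneously to the study team throughout the trial". The channels follow: "Reports will be collected via phone, email, or in person during centre visits".

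Other sections bear on the same matter:

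- Data collection: "Reasons for non-adherence (e.g. device discomfort, loss of interest) or non-retention (e.g. withdrawal, loss to follow-up) will be systematically documented".
- Concomitant care says that relevant changes in health or treatment are documented, without saying how.
- Criteria for discontinuing or modifying allocated interventions has every discontinuation recorded. Grouping of harms and reporting of adverse events lists separately those events that lead to discontinuation.
- Coding and grading of adverse events has severity and relatedness coded by blinded staff.
- Composition and role sets up no data monitoring committee; the Steering Committee looks at adverse events monthly. Interim analyses and stopping guidelines adds: "Stopping criteria will be limited to safety concerns identified by the Steering Committee".

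**The concern.** The heading promises a systematic assessment and the text beneath it supplies none for anyone in the trial. A reader of the protocol, or of a later report that follows its structure, could believe that harms were actively sought in both arms when no such enquiry is described.

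The method that is described, waiting for participants to volunteer problems, tends to miss events. Missed events make a low count look more reassuring than it is. If the tendency to volunteer differs between arms, a tabulation by arm can also show a difference that is not there or hide one that is. The Steering Committee's safety review would draw on the same incomplete information.

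The named risks are wearing the devices and the blood spot, which both arms share. What differs between arms is the encouragement to change light exposure behaviour, and no scheduled question would pick up problems arising from it.

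**Working it through.** The protocol states no harm rate, so there is no figure of its own to reproduce. The check is mainly one of text.

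**Step 1. Who is covered by the systematic section?** Eligibility criteria makes an ocular abnormality found by the optometrist a reason for exclusion. Allocation concealment and implementation says: "Group assignment is performed only after eligibility confirmation and completion of the baseline observation phase". People excluded at eye screening therefore belong to neither arm. A referral letter is also not an assessment of harm.

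**Step 2. Is there an enquiry elsewhere?** Participant timeline lists what is done at weeks 4, 10, 16 and 28: sleep, mood, cognition, frailty, physical activity, body composition and vitamin D, plus usability and acceptability at week 16. No adverse event enquiry is listed. Data collection lists none either. Its regular check-ins serve retention and completeness of data.

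**Step 3. What do the other routes catch?**

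| Route | Catches | Leaves out |
|---|---|---|
| Reasons for non-adherence or non-retention | Device discomfort that leads to non-adherence | Events in people who carry on as planned |
| Discontinuations, and events leading to them | Events severe enough to stop the intervention | Everything less disruptive |
| Changes in health status or treatment | Possibly much | Unknown, as no method or schedule is given |

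**Step 4. Illustration of size.** Input from the Sample size section: 45 per group. Assumed: true risk p per participant and capture probability r.

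*Chance that an arm reports no event* = (1 − p·r)^45.

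| True risk p | r = 1.0 | r = 0.5 | r = 0.3 |
|---|---|---|---|
| 5% | 0.95^45 = 9.9% | 0.975^45 = 32% | 0.985^45 = 51% |
| 10% | 0.90^45 = 0.9% | 0.95^45 = 9.9% | 0.97^45 = 25% |

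*Observed risk ratio when true risks are equal* = r(active)/r(control), because p cancels:

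- 0.5/0.5 = 1.0
- 0.7/0.5 = 1.4
- 0.7/0.3 = 2.33

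*Power for true risks of 10% v 30%*, two-sided 5%, normal approximation for two proportions with 45 per arm, observed risks 0.10·r and 0.30·r:

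| Capture r, both arms | 1.0 | 0.7 | 0.5 | 0.3 |
|---|---|---|---|---|
| Power | 67% | 48% | 35% | 22% |

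Equal under-capture costs events and power but leaves the expected ratio at 1 when there is no true difference. Bias needs unequal capture.

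**The case against.** The strongest reply is that spontaneous reporting is a proportionate choice for an app and wearables. The protocol describes the trial as minimal risk, safety is not among its specific objectives, and no test of harms between arms is planned. The reporting channels are the same in both arms, coding is blinded, and several domains in which harm might show, such as sleep, mood, cognition and frailty, are measured on a schedule as outcomes. All of this stands, and it limits the weight of the point.

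Four stronger readings are tempting and are not supported:

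- *That harms cannot be compared between arms.* They can be tabulated by arm; the comparison is weakened, not ruled out.
- *That all harm information comes from spontaneous reports.* The routes in Step 3 contribute some, and device discomfort is the protocol's own example of a reason that is systematically documented.
- *That the active arm will report more because it is prompted more.* Its extra prompts concern light behaviour. The control app has similar notification timing, and check-ins and reminders run in both arms. Limitations concedes only that some participants may infer their allocation. Unequal reporting is possible, not shown, and the ratios of 1.4 and 2.33 simply restate the assumed capture rates.
- *That stopping rests solely on these reports.* The stopping text gives adverse events as an example, and the Steering Committee also reviews adherence and data quality.

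The reply does not remove the mismatch between heading and content, or the lack of any stated enquiry of participants who remain in the trial. Blinded coding protects how an event is classified, not whether it is found.

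**Conclusion.** The point holds in a limited form. The section on systematic assessment describes nothing done to any randomised participant, and spontaneous report is the only stated collection route for their adverse events. The other records help but do not systematically ask about events in people who carry on. Counts will probably be incomplete. A tabulation by arm will be imprecise, and biased if reporting differs by arm, which is possible because allocation may be inferred by some.

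The size is unknown from the document. The illustration rests on assumed risks of 5% to 30%, assumed capture of 30% to 100%, and all 45 per arm being counted. The primary analysis of light exposure is unaffected. This is a minor-to-moderate point, worth acting on because the remedy is cheap.

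**What to change.** Rewrite Systematically assessed adverse events to say that a blinded assessor asks every randomised participant one open question about new health problems, in identical words in both arms, at the existing visits in weeks 10, 16 and 28. Report the answers by arm, separately from spontaneous reports. Move the referral letter to the screening or eligibility text.

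If the team prefers not to add the question, the section should say plainly that no systematic assessment is made in randomised participants, and the report should present the counts as spontaneous reports.

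Cost: a few minutes at visits that already take place, one form, and more minor events to code.

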#### Coding and grading of adverse events

All adverse events will be documented and coded by study staff according to severity (mild, moderate, severe) and relatedness to the intervention (unrelated, possibly related, probably related). Coding will be performed by personnel blinded to group allocation. No formal clinical grading system is planned, as no serious medical harms are anticipated.

#### Grouping of harms and reporting of adverse events

Harms will be grouped by seriousness (serious versus non-serious), severity and type (e.g., device-related discomfort, app-related difficulties). Any adverse events leading to discontinuation of the intervention will be recorded separately. If a serious adverse event is reported, it will be immediately reviewed by the PI and reported to the Parkway Independent Ethics Committee (PIEC), in line with ethical approval requirements.

### Ancillary and post-trial care

As the intervention involves a digital health app and wearable devices, no specific ancillary or post-trial medical care is anticipated. Any discomfort related to device wear (e.g. skin irritation) will be addressed by study staff. Participants will be covered by institutional insurance policies for study-related harm, in accordance with local regulations. No compensation is planned for non-study-related health events. Participants will receive a lay summary of the study findings at trial completion.

### Audits and inspections

#### Composition and role

Given the minimal-risk nature of the intervention (digital health app and wearable devices), no independent Data Monitoring Committee (DMC) will be established. Trial oversight will be managed by the study’s Steering Committee, which includes investigators from TUMCREATE and collaborating institutions. The Steering Committee meets monthly to review recruitment, adherence, data quality and any adverse events.

#### Trial monitoring

Trial conduct will be monitored by the institutional research governance office, which will conduct regular remote monitoring of recruitment, consent forms and data quality. Monitoring will include verification of consent, adherence to protocol and reporting of adverse events. No on-site audits are anticipated unless concerns arise.

### Protocol amendments

All substantial protocol amendments (e.g., changes to eligibility criteria, outcomes, analyses) will be reviewed and approved by the relevant IRBs prior to implementation. Updates will be made in the trial registry (ISRCTN12391932, registered 5 September 2025) and communicated to study sites, funders and participants as appropriate. Minor administrative amendments (e.g., corrections of typographical errors) will be documented in the trial master file.

## Discussion

### Strengths

This study has several strengths. It represents a novel digital behavioural intervention that specifically targets environmental light exposure as a modifiable, lifestyle-based strategy for preventive health and health promotion among older adults. To our knowledge, this is the first study to operationalise light exposure optimisation through a mHealth platform in this population. The trial is underpinned by a rigorous methodological design, employing a double-blind randomised controlled framework with allocation concealment and stratified balancing by sex, age, and recruitment site. These design features minimise selection and performance bias and enhance internal validity. A further strength is the use of a multi-modal assessment framework that combines objective measures of light exposure, physical activity, and physiological outcomes, captured using the ActLumus light logger and Garmin Vivosmart 5, with validated subjective instruments. This approach enables comprehensive outcome assessment and robust triangulation across measurement modalities. The inclusion of a pilot and feasibility phase allows refinement of study procedures, identification of implementation challenges, and optimisation of intervention delivery prior to the trial, thereby reducing operational risks and strengthening overall feasibility. Finally, recruitment through Lions Befrienders’ Active Ageing Centres situates the intervention within a real-world community context, enhancing ecological validity and supporting the potential translation of findings into community-based and public health programmes.

### Limitations

Several limitations should be considered. The digital nature of the intervention may impose a technology-related burden for some older participants, particularly with respect to device wear, data synchronisation, and mobile application use, which could affect adherence and data completeness. Furthermore, sample size assumptions were informed by effect size estimates derived from a Malaysian dataset, which may not fully reflect variability within the Singaporean older adult population and may introduce uncertainty in power estimation. Although over-recruitment has been planned, attrition related to digital literacy, participant burden, or device fatigue remains a potential risk and could reduce effective statistical power. In addition, the exclusion of individuals with cognitive impairment, ocular disease, or clinically significant depressive symptoms was necessary to ensure participant safety and reduce clinical and behavioural confounding. However, this may limit generalisability, resulting in a study sample that is comparatively healthier and more digitally capable than the broader older adult population. While blinding is strengthened by the identical visual design and navigation of the intervention and placebo applications, functional differences between versions may allow some participants to infer group allocation. Although outcome assessors remain blinded, the possibility of partial participant unblinding and residual performance bias cannot be entirely excluded.

### Publications and dissemination policy

The findings of this study will be primarily disseminated through scientific channels. Results will be published in peer-reviewed open access journals and preprints will be deposited on servers such as medRxiv to allow rapid access by the research community. In addition, anonymised participant-level data, statistical code and supporting documentation will be deposited in an open repository to ensure transparency and facilitate secondary analyses.

Authorship will follow International Committee of Medical Journal Editors (ICMJE) guidelines and no professional medical writers will be involved in the preparation of manuscripts. Author contributions will be attributed using the Contributor Role Taxonomy (CRediT).

#### Protocol and statistical analysis plan

The full trial protocol will be published in *BMC Geriatrics*. Any protocol amendments will be updated in the ISRCTN record to ensure accuracy and transparency. A separate statistical analysis plan will be finalised before data analysis and will be made openly available on the Open Science Framework (OSF). This approach ensures that analytical and statistical procedures are defined in advance and can be independently scrutinised.

## Data Availability

Upon completion of the trial and publication of the primary outcomes, anonymised participant-level data, the accompanying data dictionary, statistical code and all supporting documentation will be made available through the Open Science Framework. Data will be released under a CC-BY license, allowing unrestricted reuse with appropriate attribution. Shared materials will include de-identified data on light exposure, sleep, mood, cognition and vitamin D status, along with the relevant analytical scripts written in R and Python and documentation associated with the intervention. No application process will be required to access the dataset.

## Abbreviations

BIA: Bioelectrical impedance analysis
BL: Baseline
BMI: Body mass index
BMIS: Brief Mood Introspection Scale
CC-BY: Creative Commons Attribution license
CIE: International Commission on Illumination
DMC: Data Monitoring Committee
EDI: Equivalent daylight illuminance
EP: Endpoint
FU: Follow-up
GAMM: Generalised additive mixed model
GDS: Geriatric Depression Scale
GLMM: Generalised linear mixed model
IADL: Instrumental Activities of Daily Living
IRB: Institutional Review Board
ISRCTN: International Standard Randomised Controlled Trial Number
MAUQ: mHealth App Usability Questionnaire
MCTQ: Munich ChronoType Questionnaire
MEQ: Morningness-Eveningness Questionnaire
mHealth: Mobile Health
MoCA: Montreal Cognitive Assessment
MP: Midpoint
NIH: National Institutes of Health
OSF: Open Science Framework
PASE: Physical Activity Scale for the Elderly
PI: Principal Investigator
PIEC: Parkway Independent Ethics Committee
PSQI: Pittsburgh Sleep Quality Index
RCT: Randomised controlled trial
SCQ: Self-Administered Comorbidity Questionnaire
SIMS: Single-Item Mood Scale
SPIRIT: Standard Protocol Items: Recommendations for Interventional Trials
TAM: Technology Acceptance Model
TAT: Time above threshold
TAT250: Time above 250 lx melanopic equivalent daylight illuminance
TBT10: Time below 10 lx melanopic equivalent daylight illuminance
TFA: Theoretical Framework of Acceptability
VAMS: Visual Analogue Mood Scale
25(OH)D: 25-hydroxyvitamin D
